# The FLASSH study: protocol for a randomised controlled trial evaluating falls prevention after stroke and two sub-studies

**DOI:** 10.1186/1471-2377-9-14

**Published:** 2009-03-31

## Abstract

**Background:**

Falls are common in stroke survivors returning home after rehabilitation, however there is currently a lack of evidence about preventing falls in this population. This paper describes the study protocol for the FLASSH (FaLls prevention After Stroke Survivors return Home) project.

**Methods and design:**

This randomised controlled trial aims to evaluate the effectiveness of a multi-factorial falls prevention program for stroke survivors who are at high risk of falling when they return home after rehabilitation. Intervention will consist of a home exercise program as well as individualised falls prevention and injury minimisation strategies based on identified risk factors for falls. Additionally, two sub-studies will be implemented in order to explore other key areas related to falls in this population. The first of these is a longitudinal study evaluating the relationship between fear of falling, falls and function over twelve months, and the second evaluates residual impairment in gait stability and obstacle crossing twelve months after discharge from rehabilitation.

**Discussion:**

The results of the FLASSH project will inform falls prevention practice for stroke survivors. If the falls prevention program is shown to be effective, low cost strategies to prevent falls can be implemented for those at risk around the time of discharge from rehabilitation, thus improving safety and quality of life for stroke survivors. The two sub-studies will contribute to the overall understanding and management of falls risk in stroke survivors.

**Trial registration:**

This trial is registered with the Australian and New Zealand Clinical Trials Registry (ACTRN012607000398404).

## Background

Each year, approximately forty-eight thousand Australians are affected by stroke [1]. Despite recent advances in the management of acute stroke, including a decrease in mortality rates, stroke remains one of the leading causes of disability [1], with up to 280,000 stroke survivors in Australia experiencing disability, of whom 146,000 have a disability directly resulting from the stroke [2]. Minimising stroke sequelae is therefore important for individuals and the community.

Falls are a common adverse event among stroke survivors. It is estimated that between 14–65% fall at least once during hospitalisation [3-5] and up to 73% fall during the first six months after discharge home from hospital [6,7]. This fall rate is substantially higher than in community-dwelling older people, with approximately 30% falling in a twelve-month period [8,9]. Frequent falls appear to be more common in stroke survivors who have decreased balance or who have had a fall during their hospital admission [6].

Falls in the stroke population can have serious consequences. Estimates of soft tissue injury rate following a fall range from 24% to 48% [7,10,11]. More severe injury, such as fracture, has been reported to occur in 1% to 15% of falls in stroke survivors [7,12]. The rate of fractured neck of femur after stroke is up to two to three times higher than in the general population [13], and is in part due to the potential for decreased bone mineral density particularly in those who are unable to walk at 2 months post-stroke [14].

At present there are no published randomised controlled trials investigating the effectiveness of falls prevention strategies in stroke survivors. There is, however, evidence for the effectiveness of single and multi-factorial interventions in older community-dwelling people [15]. Exercise, including components of strength and balance, but not necessarily including a walking program, appears to be effective in preventing falls in older adults [16,17], and other interventions such as home modification and reduction in psychotropic medication have also been shown to be effective [18,19]. While it is likely that some of the approaches shown to be effective in reducing falls in older people generally may also be effective in people with stroke, there are additional stroke-specific risk factors, for example inattention or neglect, which might influence uptake and effectiveness of interventions in the stroke population. The purpose of this randomised controlled trial is to determine whether an individualised, multi-factorial intervention is effective in reducing falls in people with stroke following discharge from rehabilitation.

Fear of falling is a key factor in relation to falls [20]. Even in the absence of physical injury, a fall can have negative functional and psychological consequences, including loss of confidence or fear of falling, which can lead to activity restriction. Restricting activity may lead to further loss of strength or heightened balance impairment, which then predisposes an individual to further falls.

It has been shown that fear of falling is common in older adults [21] and although there are few published studies about the prevalence in the stroke population, it appears to be present in stroke survivors [22,23]. There is evidence to support an association between falls, fear of falling and function in older people [24] and in stroke survivors [25]. However, it is not clear whether there is a causal relationship, that is, whether a fall causes fear of falling, whether fear of falling precipitates a fall, or whether a third factor causes both. While there are several cross-sectional studies which highlight the association between falls, fear of falling and function [22,25], longitudinal studies are required to evaluate changes in fear of falling and function over time, particularly in relation to the short-term effects of a fall.

If a reduction in falls is observed, it is important to understand the mechanisms by which this has occurred. The reduction in falls may be secondary to an improvement in stability, or it may reflect increased caution when performing activities such as walking. The impact of the intervention on stability during walking is particularly pertinent, as the control of balance while walking is complex due to the inherent instability and dynamic nature of the task [26]. Examination of stability during walking will provide insight into the mechanisms by which the intervention may have an effect on reducing falls. Obstacle crossing has been shown to be a useful paradigm for exploring stability in walking following stroke [27,28].

The aims of this study are therefore threefold:

(i) to evaluate the effectiveness of a multi-factorial falls prevention program for stroke survivors returning home after rehabilitation,

(ii) to examine the temporal relationship between fear of falling, falls and function in the above population, and

(iii) to evaluate the contribution of gait impairments to the task of obstacle crossing in the context of a falls prevention program.

## Methods and design

This study consists of one main and two sub-studies. The main study is a randomised controlled trial evaluating the effectiveness of a multi-factorial falls prevention program in stroke survivors discharged home after rehabilitation. The first sub-study is a 12 month longitudinal study investigating the temporal association between falls, fear of falling and activity level, and the second sub-study is a cross-sectional study, evaluating changes in gait characteristics following stroke and their contribution to the ability to negotiate obstacles while walking.

### Randomised controlled trial

#### Participants

Stroke survivors aged forty-five years and over who have completed rehabilitation and have been discharged home will be eligible for the study if they have decreased balance or if they have fallen at any time during their hospital admission. Decreased balance is defined as a step test [29] worst leg score of less than 7 or a Berg Balance Scale [30] score of less than 49. These inclusion criteria were selected as it has been shown that decreased balance as defined above or a fall in hospital are predictors of multiple falls in the first 6 months after discharge from stroke rehabilitation [6]. Stroke sub-types will include infarct and haemorrhage (including sub-arachnoid haemorrhage) but will exclude sub-dural haemorrhage or infarct or haemorrhage due to malignancy. Those being discharged to residential care facilities and those being discharged more than one hundred kilometres from study sites will not be eligible.

#### Settings/locations

Participants will be recruited from the rehabilitation units of five health services in Melbourne and four health services in Adelaide, Australia. Participants will be assessed for eligibility by treating physiotherapy staff while still an in-patient, and if agreeable, participants will be contacted by the research team within one to two weeks of discharge. All study assessment and intervention activities will be conducted in the participant's home. Ethics approval for the study has been granted by the Human Research Ethics Committees of Melbourne Health (HREC 2006.026), Austin Health (H2006/02473), St Vincent's Health (HREC-A 066/07), Northern Health (E03006) University of South Australia (P043/06), Repatriation General Hospital (11/06), Royal Adelaide Hospital (060307), and The Queen Elizabeth Hospital (2008053). These ethics approvals cover all recruitment sites.

#### Procedures

Figure 1 depicts the study design. Participants will be assessed at baseline (following recruitment) and after 12 months in the study. Baseline assessment will include the following general measures:

**Figure 1 F1:**
[figure not shown]
**Study design – randomised controlled trial**.

(i) falls risk, using the Falls Risk for Older People in the Community (FROP-Com) [31],

(ii) functional lower limb strength measured by the five chair sit-to-stand test (5-STS) [32],

(iii) gait and balance, measured by gait velocity over 5 metres at self-selected comfortable and fast pace (5mwt-comf, 5mwt-fast) [33], Step Test (ST) [29], and Timed Up and Go with and without a secondary cognitive task (TUG-single, TUG-dual) [34,35],

(iv) activity measured by the Human Activity Profile Adjusted Activity Score (HAP-AAS) [36], and

(v) function, as measured by FIM ^® ^[37].

In addition, the following stroke specific measures will be included at baseline:

(i) participation, measured by the London Handicap Scale (LHS) [38],

(ii) fear of falling, measured by the Falls Efficacy Scale (Swedish Modification (FES-S) [39,40],

(iii) inattention, assessed by the Baking Tray Task (BTT) [41] and the Star Cancellation Test (SCT) [42],

(iv) visual field, assessed by the Visual Field Confrontation Test (VFT) [43], and

(v) frontal function as measured by the Frontal Assessment Battery (FAB) [44].

#### Randomisation

Participants will be assessed for eligibility, provided with information about the study, provide informed consent, be enrolled into the study and complete the baseline assessment prior to allocation into the control or intervention group. Participants will be assigned to the control or intervention arm of the study according to a computer generated random allocation sequence concealed from the researchers in opaque envelopes. Staff not involved in the study will undertake the sequence and concealment. The envelopes containing the allocation will be stored in one location and participants will be assigned in order of completed baseline assessment.

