#### Control group

The control group will receive usual care which consists of any activities undertaken by the participants that are recommended or administered by their treating team. In addition, control participants will receive a general information booklet on falls prevention (developed by Peninsula Health Falls Prevention Service, Victoria, Australia).

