### Fear of Falling Sub-Study

#### Procedures

In this longitudinal study, FLASSH participants from both the intervention and the control groups recruited from the sites in Melbourne, Australia will be included. This is estimated to be approximately half the overall project sample. Participants will be assessed at baseline, at four monthly intervals, and following any fall throughout the 12 month study period by a researcher blind to group allocation. Assessments will be conducted in the participant's home, and at each time-point, the following will be assessed:

(i) fear of falling (FES-S) [39,40]

(ii) gait and balance (5mwt [33], TUG (single and dual tasks) [34,35], Step Test [29])

(iii) activity (HAP-AAS [36]).

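### As described, allocation takes no account of city, although Melbourne participants get extra assessments and both sub-studies compare arms in Melbourne only; stratify by city and adjust for it

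*Protocol article*

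**What the plan says.** **Allocation (protocol article, Randomisation).** Participants are assigned "according to a computer generated random allocation sequence concealed from the researchers in opaque envelopes", prepared by staff outside the study. Then: "The envelopes containing the allocation will be stored in one location and participants will be assigned in order of completed baseline assessment". City and site play no part in the rule as written.

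**Recruitment (Settings/locations).** "Participants will be recruited from the rehabilitation units of five health services in Melbourne and four health services in Adelaide, Australia".

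**Comparator (Control group).** Controls receive "usual care which consists of any activities undertaken by the participants that are recommended or administered by their treating team".

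**Assessments.** For the main trial, the section Procedures states: "Participants will be assessed at baseline (following recruitment) and after 12 months in the study". For the Fear of Falling Sub-Study, its own Procedures section states: "FLASSH participants from both the intervention and the control groups recruited from the sites in Melbourne, Australia will be included". It adds: "Participants will be assessed at baseline, at four monthly intervals, and following any fall throughout the 12 month study period by a researcher". Those visits repeat the FES-S, gait speed, Timed Up and Go, Step Test and HAP-AAS, all of which the section Outcomes lists as secondary outcomes of the main trial.

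**Sub-study comparisons.** The Obstacle Crossing Sub-Study also draws only on Melbourne sites. The statistical sections of both sub-studies include a comparison of intervention with control.

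**The concern.** Read plainly, one list is consumed across two cities in whatever order baseline assessments finish. The article itself makes the cities differ. Melbourne participants are seen and tested more often on measures that are also main-trial outcomes, so practice effects and study contact can differ by city. Usual care follows the local treating team, and much of the intervention is referral to other providers (Table 1), so the control condition and the delivery of referrals may also vary by place.

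A list balanced over the whole trial does not secure balance within a city. Two things are at stake:

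- In the main trial, a chance gap between arms in the share from Melbourne carries any city difference into the treatment contrast and adds avoidable noise.
- In the sub-studies, the arms are compared within the Melbourne subset, where the list as described controls nothing.

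**Working it through.** **1. The plan's own figures.** The article gives no figure for balance by city. The inputs come from Sample Size: 75% versus 50% fallers, 85 per arm before dropout, 107 per arm and 214 in total enrolled. The 85 reproduces with the continuity-corrected two-proportion formula. The uncorrected formula gives n = (1.96 × √(2 × 0.625 × 0.375) + 1.2816 × √(0.75 × 0.25 + 0.50 × 0.50))² / 0.25² = 76.7. The correction gives (76.7/4) × (1 + √(1 + 4/(76.7 × 0.25)))² = 84.5, rounded up to 85. The planned difference of 25 points is the yardstick in step 4.

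**2. Spread of the Melbourne share.** Assume 107 of the 214 are from Melbourne (the article says approximately half) and the list is forced to 107:107 overall but ignores city. The number of Melbourne participants in one arm is then hypergeometric:

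- Variance = 107 × 0.5 × 0.5 × 107/213 = 13.44, so SD = 3.67 people.
- The between-arm difference in Melbourne share is (2k − 107)/107, with SD = 2 × 3.67/107 = 6.9 percentage points.
- The 95% limit is 1.96 × 6.85 = 13.4 points.

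The result is not sensitive to the assumed share. With 80 Melbourne participants the count SD is 3.55 and the share SD is 2 × 3.55/107 = 6.6 points.

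**3. Chance of a visible gap.** A split of 59:48 or worse is a gap of at least 11/107 = 10.3 points. Its hypergeometric probability is 0.171.

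**4. Effect on the primary contrast.** The shift in the arm difference is the gap in Melbourne share times the city difference in faller proportion. At the 95% limit, an assumed city difference of 5 points gives 0.05 × 13.4 = 0.7 points, and one of 20 points gives 0.20 × 13.4 = 2.7 points, against the planned 25.

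**5. Sub-studies.** These figures treat the participants as a random subset of those randomised. The efficiency of a split s relative to 50:50 is 4s(1 − s).

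| Sub-study and split | Simple randomisation | 107:107 overall, city ignored | Melbourne list balanced | Efficiency kept |
|---|---|---|---|---|
| Fear of falling (80), 60:40 or worse | 9.3% | 3.4% | not calculated | 96% at 60:40 |
| Obstacle crossing (30), 19:11 or worse | 20.0% | 16.7% | about 13% | 93% at 19:11 |
| Obstacle crossing (30), 20:10 or worse | 9.9% | 7.5% | about 5% | 89% at 20:10 |

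**The case against.** The case on the other side has four parts.

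- **The single list is inferred.** Central storage and ordered assignment are compatible with separate envelope sets per city, and a condensed article may leave stratification to the full protocol. This stands as a caution. However, the article states a rule, with one sequence and one order of use, and a single queue is its plainer reading.
- **Unstratified randomisation is valid.** The test's error rate already covers chance imbalance, and the extra Melbourne visits apply to both arms. This stands: the loss is precision and chance confounding, and a city term in the model would recover most of it.
- **Stratification does little for the obstacle sub-study.** Its volunteers are approached at 12 months, so the split also depends on retention and consent. A Melbourne-balanced list moves 20:10 or worse only from 7.5% to about 5%, and that analysis already plans to adjust for covariates found to differ between the arms. This stands. The fear-of-falling sub-study is likewise mainly about timing between falls and fear, where arm balance matters less.
- **Service could be argued as well as city.** Usual care may vary among all nine services. That is fair, but the difference in assessment schedule and the sub-study restriction follow city.

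A reader might also infer that different therapists work in each city. Home visits in two cities make that plausible, but the article identifies the physiotherapists by role only and never says so. The point does not rely on it.

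**Conclusion.** The point holds as a modest, optional improvement to a stated design choice. As the article reads, balance by city is left to chance in a trial where assessment schedule and sub-study membership depend on city. The size is a standard deviation of about 6.9 points in the between-arm difference in Melbourne share, and a 17% chance of a gap of about 10 points or more. This assumes half the sample is from Melbourne and the list is balanced only overall. The plausible shift in the primary contrast, 0.7 to 2.7 points against 25, also rests on the assumed city differences of 5 to 20 points.

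Three stronger readings are not supported: that the randomisation is invalid or biased, that the list is known to be unstratified, and that a badly lopsided obstacle-crossing sample is to be expected or would be prevented by stratifying.

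**What to change.** State whether the sequence is stratified by city. If it is not:

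1. Have the independent staff prepare one sequence for Melbourne and one for Adelaide, each in randomly permuted blocks of varying size, with both sets of envelopes in the same central store. Each participant receives the next envelope of their own city.
2. Include city in the negative binomial model for falls and in the main trial's between-arm models for secondary outcomes.
3. If allocation has already begun, use city-specific lists for the remaining participants and keep the city term for everyone.

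The cost is a second computer-generated list and one model term, with no extra participants, visits or staff. The downside is slightly more predictable allocation from blocking, which varying block sizes limit. The change balances the Melbourne pool at randomisation, to within half a block. It does not fix the arm split among those who later volunteer for obstacle crossing.

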#### Intervention

The intervention consists of a multi-factorial falls prevention program implemented by a physiotherapist including:

1) an individualised home exercise program with strength, balance and walking components based on the Otago Exercise Programme [45,46]. Exercise selection and dosage will be determined by the research physiotherapist and administered in the participant's home at a visit following the baseline assessment. Exercises will be selected to address balance and mobility problems identified in the baseline assessment and will be tailored to the level of each participant. The program will be monitored and modified by the physiotherapist at two subsequent home visits during the 12 month study period. Participants will be advised to undertake the exercise program at least five times per week. Participants will be provided with an exercise recording sheet to indicate completed exercises, and adherence to the exercise program will be assessed by the physiotherapist at the review visits.

2) falls risk minimisation strategies based on the falls risk factors identified in the baseline assessment in the context of falls prevention activities already in place, together with participant preference. Falls risk factors will be identified using the FROP-Com, which is designed to identify the level of falls risk associated with the common falls risk factors in community-dwelling older persons. Interventions may include, for example, referral for vision assessment and correction, changes to footwear, change in walking aid, referral for home modifications, medication review, and continence review and management. Guidelines for this component of the intervention are summarised in Table 1.

**Table 1 T1:** Guidelines for intervention options for FLASSH study: falls risk minimisation

**Risk factor**	**Intervention options if risk factor identified**
History of falls/falls injuries	Referral to GP Appropriate acute management if injury recent
Medications (number)	Refer to GP for medication review
Medications (associated with increased falls risk)	Refer to GP/specialist for medication review
Medical conditions (associated with increased falls risk)	Refer to GP/specialist for review
Sensory loss: vision	Brochure on lighting and home safety Refer to optometrist Refer to Ophthalmologist via GP Refer to Vision Australia (includes mobility training and aids for visually impaired) Refer to OT for home assessment Refer to GP
Sensory loss: hearing	Refer to audiologist
Sensory loss: somatosensory	Refer to podiatrist Refer to GP
Feet and footwear	Refer to podiatrist Provide information about good footwear and falls prevention
Cognitive status	Refer to GP Memory Clinic referral in consultation with GP if memory problems have not been investigated Referral to OT for strategies to facilitate memory and/or home assessment
Continence	Refer to GP Continence clinic referral Refer to physiotherapist Refer for OT home assessment/functional assessment, including need for commode
Nutritional status	Provide brochure on nutrition Refer to dietician GP referral
Environment	Provide with information pamphlet on safety in the home Refer for OT home assessment/functional assessment and training
Function	Refer to OT for home assessment/functional assessment and training Refer to Physiotherapist for assessment and exercise to improve function Referral for support services
Functional behaviour	Refer to physiotherapist, OT, GP
Balance	Home exercise program Referral to Physiotherapist Referral for OT for a home assessment Referral to GP for further investigation
Gait and physical activity	Home exercise program Referral to Physiotherapist Referral for OT home assessment/functional assessment and training Brochure on tips for walking
Osteoporosis risk	Refer to GP for consideration of calcium and/or vitamin D supplements Refer to dietician Hip protectors
Additional options for preventing falls injury	Hip protectors Personal alarm

GP: General practitioner

OT: Occupational therapist

3) education of the patient and their carer about identified falls risk factors and risk minimisation, including provision of information in verbal and written forms. This will be undertaken by the physiotherapist implementing the exercise program.

4) injury risk minimisation strategies for those identified as having a high risk for fracture based on falls risk, delayed walking post-stroke or previous diagnosis of osteoporosis. These strategies will include prescription of hip protectors and liaison with the participant's general practitioner for consideration of vitamin D and calcium supplementation.

Participants in the intervention group will continue to receive usual care which consists of any activities undertaken by the participants recommended or administered by their treating team. In addition, intervention participants will receive a general information booklet on falls prevention (developed by Peninsula Health Falls Prevention Service, Victoria, Australia).

